#### 9.4.3 ANALYSIS OF THE SECONDARY ENDPOINT(S)

Analysis of secondary end points will follow procedures described in section 9.4.2.

---

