| Staff Turnover rate from Baseline to 3 months                            | Staff turnover will be assessed by asking directors: "How many total staff work at center?" "How many staff have left, quit, or been fired in the past 3 months?", and "how many of those staff have you replaced in the past three months or are currently trying to replace?". Questions will be asked at baseline and 3 month follow-up. Turnover rate for a center will be expressed as: $((\# \text{ staff left job} - \# \text{ staff not need replacing}) / (\# \text{ total staff})) * 100 = \% \text{ turnover}$ . | A study specific survey will measure 4 types of turnover: voluntary (by choice), involuntary (reasons beyond their control), external (leaves employer), and internal (changes job with employer). Turnover rate will be calculated using data provided by the employer. The precise rate (i.e., turnover events/workers employed in a fiscal year) will be calculated. |
| Tertiary/Exploratory                                              |                                                                                                                                                                                                                                                                                                                                                                                                                                                                                                                             |                                                                                                                                                                                                                                                                                                                                                                         |

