#### 9.4.2 ANALYSIS OF THE PRIMARY ENDPOINT(S)

Our primary analyses will involve testing change in the total score from CD-RISC between SMART and control groups at 3 months. Using maximum likelihood methods, we will use multi-level linear mixed models (PROC MIXED) that include random effect for cluster to account for covariance between participants within the same center as well as fixed effects for time (0, 3, 9, 15 months), trial arm (SMART or matched attention control), time\*arm interaction. To assess the primary endpoint from this mixed model we will include a contrast statement to calculate mean and 95% confidence intervals to estimate change for our primary outcome from baseline to 3- (primary endpoint), 9-, and 15-months (secondary endpoints). A proper error covariance structure will be chosen based on model fit indicated by model likelihood, Akaike Information Criterion and Bayesian Information Criterion. Residuals will be examined to check the assumptions of models. To further explore the effect of the intervention, sensitivity analyses will be conducted that adjust for baseline variables distributed differently between groups and to examine completers only. Similar analyses will be completed for secondary outcomes. Baseline variables including center and worker demographics will be included as covariates to assess their potential moderating effect

All analyses will be conducted using the intention-to-treat principle, in which all available data on all randomized participants are included. This approach minimizes bias if individuals drop out of the trial for different reasons. Every effort will be made to obtain follow-up data on all participants randomized, whether or not they follow their assigned treatment. Our maximum likelihood approach assumes that any missing outcome data are missing at random (i.e., missing data including that due to drop-out can be dependent on any previously observed outcomes or treatment assignment). With this approach, we use all data that have been collected without regard to whether data are missing for a participant at another visit, including drop-out, and without explicit imputation of missing data. If the combined rate of missingness on variables is above 5%, we will impute missing endpoint data using multiple imputation

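### Center-level turnover is sent to a participant-level change model; one record per center with baseline adjustment would use the same data better

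*Protocol*

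**What the plan says.** Section 9.4.3 is one sentence: "Analysis of secondary end points will follow procedures described in section 9.4.2". Section 9.4.2 adds "Similar analyses will be completed for secondary outcomes". Neither makes an exception for endpoints measured on centers.

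The 9.4.2 model is a linear mixed model with a "random effect for cluster to account for covariance between participants within the same center" and "fixed effects for time (0, 3, 9, 15 months), trial arm (SMART or matched attention control), time\*arm interaction". The treatment effect is read from a contrast for change from baseline.

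Section 3 defines the turnover endpoint at a different level. "Staff turnover will be assessed by asking directors"; "Turnover rate for a center will be expressed as" a percentage of total staff; and "Questions will be asked at baseline and 3 month follow-up". Absenteeism, in the same table, combines staff and director items into a value for the center, without saying how.

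The power statement in section 9.2 concerns CD-RISC only.

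**The concern.** Turnover gives one number per center at two of the four modelled times. There are no participants within a center for the random effect to describe, and the text does not say which records enter the model.

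An analyst following 9.4.3 literally has two routes. The first uses one row per center per time; the random center effect then becomes a repeated-measures effect and the contrast compares center change scores. That is a sound test, but it subtracts a baseline value that may predict follow-up poorly. Turnover over three months in centers that may employ as few as 8 staff is a small count, so a weak correlation is plausible. The second route keeps the participant file and repeats the center value on each worker's row, which counts one observation several times.

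At stake is the precision, and on the second route the validity, of a comparison that the synopsis lists as a secondary objective.

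**Working it through.** **The plan's own power figure.** Inputs from section 9.2: 40 centers per arm, 8 workers per center, effect size 0.35, ICC 0.10, alpha 0.05 (two-sided assumed). The usual design effect, 1 + 7 × 0.10 = 1.70, gives 92.4%. Scaling the effect to the within-center SD gives a design effect of 1.70 / 0.90 = 1.889, hence 320 / 1.889 = 169.4 effective workers per arm. Power is Φ(0.35 × √(169.4/2) − 1.96) = Φ(1.26) = 89.6%, matching the stated 90%. The same formula reproduces all 36 cells of the power table (largest difference 0.005) and the 84% and 82% after attrition (34 and 32 centers per arm). The 90% therefore rests on eight worker scores per center and says nothing about 40 single values per arm.

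**Relative efficiency.** Let center values have the same SD at both times and correlation r between baseline and 3 months. In units of that variance:

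- unadjusted change: 2(1 − r)
- 3-month value adjusted for baseline: 1 − r²
- ratio: (1 − r²) / [2(1 − r)] = (1 + r)/2

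This is below 1 for every r below 1, so only the size of the loss depends on r.

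**Power.** Noncentral t, 40 against 40 centers, two-sided 0.05, effect 0.35 SD of center values (assumed; the protocol gives no effect size for turnover). The noncentrality is 0.35 × √20 / √(variance factor). At r = 0 this is 1.565/√2 = 1.107 for change and 1.565 for the adjusted comparison.

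| r | Efficiency of change | Power, change | Power, adjusted |
|---|---|---|---|
| 0 | 0.50 | 19% | 34% |
| 0.3 | 0.65 | 26% | 37% |
| 0.5 | 0.75 | 34% | 43% |
| 0.7 | 0.85 | 51% | 58% |

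The effect detectable with 80% power is 0.89 SD (change) against 0.63 SD (adjusted) at r = 0, and 0.63 against 0.54 at r = 0.5.

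**Simulation with turnover counts.** All inputs are assumed: about 14 staff per center, turnover halved in one arm, and between-center SD of 0.4 or 0.9 on the logit scale. Ranges are over the two SDs.

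| 3-month turnover | Change | Adjusted, linear | Adjusted, overdispersed binomial |
|---|---|---|---|
| 6% | 34–42% | 61–63% | 63–65% |
| 12% | 64–68% | 84–91% | 86–91% |
| 20% | 85–87% | 96–98% | 97–98% |

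Simulated r ran from about 0.1 to 0.6. With no effect, the change and adjusted linear analyses rejected in 4–6% of trials. On center rows, the mixed-model t statistic matched a two-sample t test on center change (largest difference 4e-05).

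**If center values were copied to 8 worker rows.** Treating the copies as independent understates the standard error by √8, so type I error is 2 × [1 − Φ(1.96/√8)] = 2 × [1 − Φ(0.693)] = 0.49. A simulation with the random center effect gave 0.63. The random effect absorbs a center's average level but not its copied change.

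**The case against.** The strongest reply is that nothing here is invalid. Centers are the unit of randomization, the rate is defined for a center, and the promise of similar analyses for secondary outcomes leaves room to use one row per center. The two missing time points simply drop out, and type I error is then close to 5%. All of that stands.

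A reader might infer three stronger conclusions that the documents do not support:

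- **That the turnover test will be anti-conservative.** No section says center values will be copied to workers. The 0.5 to 0.6 error rate is conditional on that implementation.
- **That a linear model for a percentage is the fault.** The baseline-adjusted linear and binomial analyses were within about 3 points of each other. The loss comes from the unadjusted change contrast.
- **That much power is certainly wasted.** This depends on r, which is not given. At 0.35 SD the gap is 15 points at r = 0 but 7 at r = 0.7.

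The stakes are also limited. Turnover and absenteeism do not appear among the hypotheses in section 9.1, no power is claimed for them, and even the better analysis has only 34–43% power at 0.35 SD for r up to 0.5. Absenteeism is less clear, because staff report their own missed days and a participant-level analysis would be possible.

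It could also be said that record level and covariates belong in a statistical analysis plan. But section 9.4.3 does not leave the method open; it assigns one, and a better one is available from data already to be collected.

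**Conclusion.** For turnover the concern holds as a point of specification and efficiency. The model assigned by 9.4.3 is not specified for one value per center. Its natural center-level form is a valid change-score comparison with relative efficiency (1+r)/2 against baseline adjustment. That the loss exists requires only r below 1 and similar variances at the two times. Its size is not fixed by the documents: half the information at r = 0, a quarter at r = 0.5, 15% at r = 0.7. In the simulated cases the loss was 9 to 29 power points, under assumed turnover rates, center sizes and effect.

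The 90% power in section 9.2 should not be read as covering this endpoint. False replication is a possibility that the wording should exclude, not something the protocol plans. This is a free improvement to consider; it does not affect the primary analysis.

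**What to change.** Amend section 9.4.3 to say:

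- Turnover, and absenteeism if it is kept as a center value, is analysed with one record per center.
- The 3-month value is regressed on arm and the center's baseline value, with robust standard errors.
- For turnover, a count model with the number of staff as denominator and overdispersion allowed is the sensitivity analysis.
- The 9.4.2 model applies to worker-level endpoints only.

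Add to section 9.2 that the stated power is for CD-RISC and not for center-level endpoints. The cost is wording in the protocol or statistical analysis plan, best settled before any unblinded analysis. Baseline and 3-month turnover and the staff count are already collected.

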#### 9.4.4 SAFETY ANALYSES

N/A

---

#### 9.4.5 BASELINE DESCRIPTIVE STATISTICS

While randomization should be sufficient to balance baseline characteristics of the staff and directors recruited to each arm, we will compare age, race/ethnicity, weight, income, education, years working at ECE center, center size, and center cost (per week) between study arms using simple mean or frequency comparisons. If group differences are deemed statistically significant and clinically meaningful, we will fit models with and without covariates for assessment.

---

#### 9.4.6 PLANNED INTERIM ANALYSES

No interim assessment of primary/secondary endpoint is planned.

---

#### 9.4.7 SUB-GROUP ANALYSES

Exploratory analyses will include examination of the moderating effects of age, race/ethnicity, income, education, readiness for change, center size. Significant interactions between sub-group and study arm will be examined in more detail to summarize the relational impact (e.g. what age group shows most change) and meaningfulness (statistical and clinical significance) in greater detail.

---

#### 9.4.8 TABULATION OF INDIVIDUAL PARTICIPANT DATA

Individual participant data will be compiled by measure and timepoint for analysis and summary statistics, but all reports and manuscripts will only include group level summaries of available data. After follow-up a public dataset will be made available. All identifiable information will be removed from public data.

---

#### 9.4.9 EXPLORATORY ANALYSES

Exploratory analyses will follow protocols described in section 9.4.2. Exploratory models will include an additional interaction term to assess the moderating impact of:

- Age –
  - Continuous
  - Categorical (under 30, 30-55, 55+)
- Race/Ethnicity – based on previous work will likely be defined as:

- non-Hispanic White, non-Hispanic black, Hispanic
  - non-Hispanic white and BIPOC
- Income
  - 7-level “treated” as continuous
  - Median split
- Education: based on previous work will likely define as:
  - 2-level (high school/some college vs college degree+)
- Readiness for change
  - continuous score based on 20-Likert-type items related to intervention components

## 10 SUPPORTING DOCUMENTATION AND OPERATIONAL CONSIDERATIONS

### 10.1 REGULATORY, ETHICAL, AND STUDY OVERSIGHT CONSIDERATIONS

#### 10.1.1 INFORMED CONSENT PROCESS

##### 10.1.1.1 CONSENT/ASSENT AND OTHER INFORMATIONAL DOCUMENTS PROVIDED TO PARTICIPANTS

The following consent materials are submitted with this protocol:

- Director consent
- Staff consent

##### 10.1.1.2 CONSENT PROCEDURES AND DOCUMENTATION

Consent will be completed digitally through IRB approved Qualtrics survey. After screening, an information call, and verbal agreement participants will be sent a link to the online consent.

#### 10.1.2 STUDY DISCONTINUATION AND CLOSURE

Given the minimal risk associated with this intervention study, it is highly unlikely that an accumulation of excess SAEs would prompt halting the trial. However, we will monitor SAE rates in all participants, with particular attention to those rated as severe and associated with study participation. If larger than expected SAE rates occur the DSMP, together with the MPIs, will alert the IRB and NCCIH that halting or modifications are under review by the study team.

#### 10.1.3 CONFIDENTIALITY AND PRIVACY

Subject confidentiality is strictly held in trust by the investigators, study staff, and the sponsoring agency. This confidentiality is extended to any study information relating to subjects. The study monitor or other authorized representatives of the sponsor may inspect all study documents and records required to be maintained by the investigator, including but not limited to 0, 3, 9, and 15 month assessments for the study subjects. The study site and PIs will permit access to such records.

A number of steps will be taken to protect participants against any possible risks. Data will be collected by trained and experienced research assistants with clearly established data collection procedures. All study personnel will also be required to complete regular human subjects' protection certification as well as the good clinical practice for social/behavioral research certification available at the University of North Carolina, Chapel Hill (CITI training). Data collection trainings will reiterate the importance of protecting subjects against potential risks and maintaining confidentiality of all data.

Additionally, collection of data is for research purposes only, and is kept in strict confidence by study personnel. To help protect confidentiality, all participants will be assigned a numeric ID. All data collection tools will use that ID to minimize the appearance of identifiers (e.g., subject name) on paper forms and in electronic data tables. Hard copies of forms (if any) will be stored in a locked file cabinet at the UNC Center for Health Promotion and Disease Prevention.

Electronic data files will be stored on UNC's secure password-protected servers. UNC's administration policies and programming coding standards are in compliance with current security regulations. To ensure data security of web-based data, the UNC network utilizes a secure authentication mechanism, the Transport Layer Security (TLS) system, which is the successor to the Secure Sockets Layer (SSL) protocol. This security mechanism supports encryption in both directions (to and from the website) and protects your username and password and also protects data with network encryption. Since TLS is web-based, it provides encryption of data across all devices including mobile devices such as smartphones.

#### 10.1.4 FUTURE USE OF STORED SPECIMENS AND DATA

Public use study data and associated documentation will be deposited in the Research Data Management Core's UNC Dataverse. Dataverse is a digital archive for scholarly materials produced by members of the University of North Carolina at Chapel Hill community. Dataverse provides searchable study-level metadata for dataset discovery. Dataverse assigns DOIs as persistent identifiers and has a robust preservation plan to ensure long-term access. Data will be discoverable online through standard web search of the study-level metadata as well as the persistent pointer from the DOI to the dataset.

Cleaned data used to assess study aims from this project will be made available as soon as possible, and no later than the time of publication or the end of the funding period, whichever comes first. The duration of preservation and sharing of the data will be a minimum of 10 years after the funding period.

There are no anticipated factors or limitations that will affect the access, distribution or reuse of the survey data generated by the proposal. Upon the conclusion of data collection for this study, all direct respondent identifiers (e.g., names and addresses) will be expunged and securely maintained in a separate control file for future contact purposes. Access to participants' identifying information is restricted to approved staff solely as part of their project duties within a secure computing environment. Deidentification will be finalized by the end of data processing, preceding the public release.

#### 10.1.6 SAFETY OVERSIGHT

The Independent Monitoring Committee (IMC) for this study is comprised of [name], [name], and [name]. The members of the IMC are not part of the key personnel involved in this grant and work independently of the PIs, Drs. [name] and [name]. No member of the Committee has collaborated or co-published with the PIs within the past three years. [name] has experience conducting physical activity intervention in adults. [name] is a PhD prepared

biostatistician and has previously served on an IMC (DSMB). [name] has experience in mindfulness research and is a clinical psychologist.

Progress and safety will be reviewed monthly, with reports, including summaries of recruitment, Adverse Events, withdrawal, and attrition. These reports will be provided to the IMC quarterly. An annual report will be compiled and will include a list and summary of AEs. In addition, the annual report will address (1) whether AE rates are consistent with pre-study assumptions; (2) reasons for dropouts; (3) whether all participants met eligibility criteria; (4) whether continuation of the study is justified based on current enrollment and withdrawal rates; and (5) conditions whereby the study might be terminated prematurely. The annual report will be sent to the Independent Monitor(s) and will be forwarded to the IRB and NCCIH. The IRB and other applicable recipients will review progress of this study on an annual basis.

---

#### 10.1.7 CLINICAL MONITORING

N/A (see 10.1.8 Quality Assurance and Quality Control)

---

#### 10.1.8 QUALITY ASSURANCE AND QUALITY CONTROL

Quality control (QC) procedures will be implemented as follows:

##### Informed consent

- Study staff will review both the documentation of the consenting process as well as a percentage of the completed consent documents. This review will evaluate compliance with GCP, accuracy, and completeness. Feedback will be provided to the study team to ensure proper consenting procedures are followed.

##### Source documents and electronic data

- Data will be initially captured on source documents (see Section 10.1.9, Data Handling and Record Keeping) and will ultimately be entered into the study database. Data will be initially captured on source documents (see Section 10.1.9, Data Handling and Record Keeping) and will ultimately be entered into the study database. To ensure accuracy, site staff will compare a representative sample of source data against the database, targeting key data points in that review.

##### Intervention Fidelity

- Consistent delivery of the study interventions will be monitored throughout the intervention phase of the study. Procedures for ensuring fidelity of intervention delivery are described in Section 6.2.1, Interventionist Training and Tracking.

##### Protocol Deviations

- The study team will review protocol deviations on a regular basis and will implement corrective actions when the quantity or nature of deviations are deemed to be at a level of concern. Should independent monitoring become necessary, the PI will provide direct access to all trial related sites, source data/documents, and reports for the purpose of monitoring and auditing by the sponsor/funding agency, and inspection by local and regulatory authorities.]

Our quality control and assurance plans fall into the following categories:

Staff training

- In year 1, study staff will be trained to manage the delivery of the SMART program and attention control physical activity program. A primary and back-up member of the research staff will complete all trainings. Staff manuals, which outline protocols and procedures for intervention delivery, will be developed for each intervention arm as we have done in our previous trials.
- For SMART, research staff will complete the Trainer Skills Intensive program (~6 months), conducted by Drs. [name] (Co-I) and [name] (collaborator), to become a certified resilience trainer. This standardized program provides the knowledge and skills of the science and art of resilience. The Certified Resilience Training Program has successfully trained over 150 resilience trainers.
- For the attention control, similar to our prior studies using physical activity education interventions, a detailed manual of procedures for the physical activity intervention will be provided to research staff that contains descriptions of all intervention components. Staff will receive standard training and certification which includes a mix of written materials, didactic sessions with the investigative team, and hands-on/practice-based exercises (~6 months).

